**Fig. 3 Fig3:**
[figure not shown]
Locations of acupoints: SP9 (*yinlingquan*), on the medial side of the shank, at the depression posterior and inferior to the medial condyle of the tibia. GB34 (*yanglingquan*), on the lateral side of the lower leg, in the depression anterior and inferior to the head of the fibula. EX-LE04 (*neixiyan*), in the depression located on the medial side of the patellar ligament. EX-LE5 (*waixiiyan*), in the depression located on the external side of the patellar ligament

Referring to previous studies [23, 24], the acupuncture procedures are as follows: after the skin has been cleaned with tincture of iodine and alcohol, sterile acupuncture needles (0.25 mm in diameter, 25 or 40 mm long, Hwatuo, Suzhou, China) will be inserted for 0.5–1.5 *cun* and gently twisted, lifted and thrust with even amplitude, force and speed for four to six times until *deqi* is obtained (soreness, numbness, distension and heaviness). The needles will then be left in place for 30 min, during which manipulation will be applied every 10 min. Every patient will receive five treatments per week for 2 weeks.

#### Sham acupuncture group

The selected non-acupoints in the sham acupuncture group include NP-1 (2–3 cm behind GB34), NP-2 (2–3 cm behind SP9), NP-3 (4 *cun* above the base of the patella and the midpoint between the Spleen Meridian and Stomach Meridian) and NP-4 (4 *cun* above of base of the patella and the midpoint between the Gallbladder Meridian and Stomach Meridian) (Figs. 4 and 5). The acupuncture procedure is the same as that in the verum acupuncture group.

**Fig. 4 Fig4:**
[figure not shown]
Locations of sham acupoints: NP-1 (sham acupoint 1), 2–3 cm behind GB34. NP-2 (sham acupoint 2), 2–3 cm behind SP9

**Fig. 5 Fig5:**
[figure not shown]
Locations of sham acupoints: NP-3 (sham acupoint 3), 4 *cun* above the base of the patella and the midpoint between the Spleen Meridian and Stomach Meridian. NP-4 (sham acupoint 4), 4 *cun* above the base of the patella and the midpoint between the Gallbladder Meridian and Stomach Meridian

#### Waiting-list group

In the waiting-list group, participants will receive no treatment within 2 weeks. After 2 weeks’ observation, patients will receive 10 verum acupuncture treatments or 2 weeks’ celecoxib treatment for free as compensation.

#### Concomitant medications and other interventions

Patients will be instructed not to take any caffeine (such as tea and coffee), and not to take any other medications or use interventions such as weight-loss techniques and physical activity, etc. for KOA during this study. In cases of severe knee pain, ibuprofen (300 mg per capsule with sustained release) will be allowed as rescue medication and should be recorded on the knee-pain diary. After the end of the study, patients will be taught weight-loss techniques and physical activity.

Patients are also asked to record the name, dose, date and the exact time of the medications used, and to report to the researcher if they take any regular medications during the study.

#### Patient safety

Adverse events caused by acupuncture, such as pain, bleeding, fainting or other severe events, should be processed immediately and recorded in detail in the case report form.

### MRI data acquisition

MRI data will be acquired with a 3.0-T magnetic resonance scanner (GE 3.0 T MR750, Wauwatosa, WI, USA) with a 16-channel phase-array head coil at the MRI Center at the University of Electronic Science and Technology of China. Participants are asked to stay awake and to keep their heads still during the scan, with their eyes closed and ears plugged. Participants are asked to keep relaxed and not to think of anything particular during the whole scan.

Prior to the blood-oxygen-level-independent (BOLD) resting-state functional images, a high-resolution structural image for each subject will be acquired using a three-dimensional MRI sequence (3DT1) with a voxel size of 1 mm^3^, employing an axial fast spoiled-gradient-recalled sequence (repetition time 6.008 ms, echo time 1.7 ms, data matrix, 256 × 256; field of view, 256 × 256 mm^2^). The BOLD resting-state functional images will be obtained with echo-planar imaging (31 contiguous slices with a slice thickness of 5 mm, repetition time 2000 ms, echo time 30 ms, flip angle 90°, field of view, 240 × 240 mm^2^; data matrix 64 × 64, total volumes 205). After the BOLD-fMRI scan, diffusion tensor imaging (DTI) sequences with single-shot echo-planar imaging will be acquired to detect any possible abnormality of the white matter with the following parameters: field of view 256 × 256 mm^2^, repetition time 8500 ms, echo time minimum, matrix = 128 × 128, slice thickness 2 mm, 78 continuous axial slices with no gap. Two diffusion-weighted sequences will be acquired using gradient values b = 0 s/mm^2^ and b = 1000 s/mm^2^ with the diffusion sensitizing gradients applied along 64 non-linear directions.

### Outcome measurement

The clinical outcome will measure patients’ knee pain and physical function, quality of life (QOL) and emotional status. All measurement will be performed at the baseline and at the end of the treatment. The primary outcome measurements are the Visual Analog Scale (VAS)[25] and short-form of the McGill Pain Questionnaire (SF-MPQ) [26]. The VAS is a 10-point scale selected to quantitatively evaluate the level of knee pain during the study. It scores from “0 (none),” “about 2 (mild),” “around 5 (moderate),” “almost 8 (severe),” and “nearly 10 (unbearable)” spaced along the continuum. The SF-MPQ focuses on evaluating the sensory and affective components of knee pain in the last 2 weeks. It mainly consists of 15 descriptors (11 sensory and four affective) rating on an intensity scale as “0 = none,” “2 = moderate,” and “3 = severe.” A higher total score indicates more severe pain.

The secondary outcomes are the Western Ontario and McMaster Universities Osteoarthritis Index (WOMAC) [27], the Attention Test Scale (ATS), the Pain Assessment of Sphygmomanometer (PAS) [28] and the 12-Item Short Form Health Survey (SF-12) [29]. The WOMAC is a self-administered questionnaire consisting of 24 items divided into three subscales: pain (five items), stiffness (two items) and physical function (17 items). These measurements will be used to subsidiarily evaluate the symptom and QOL improvement at the baseline and the end of treatment.

Furthermore, to investigate the influence of emotional state on the brain activity, the Self-rating Anxiety Scale (SAS) [30] and the Self-rating Depression Scale (SDS) [31] will be used at the baseline and the end of treatment. To ensure the consistency of acupuncture manipulation, the *deqi* scale will be performed after each acupuncture treatment (Fig. 2). The *deqi* scale is derived from the Chinese version of the modified Massachusetts General Hospital Acupuncture Sensation Scale (C-MASS) [32, 33], the validity and reliability of which have been tested [33, 34]. The scale will be used to evaluate the needle sensations (including soreness, numbness, fullness, heaviness, aching), respectively. All the evaluations are evaluated by two trained, licensed physicians.

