**Methods/design:**

In total, 108 participants diagnosed with KOA will be recruited. They will be blinded to group assignment and randomized to either verum acupuncture, sham acupuncture or waiting-list groups with 36 patients in each group. Each patient in the acupuncture group will receive five treatments per week for 2 weeks. This study will focus on detecting the cerebral functional connectivity changes elicited by acupuncture treatment. The Visual Analog Scale and the short form of the McGill Pain Questionnaire, the Western Ontario and McMaster Universities Osteoarthritis Index, the Attention Test Scale, the Pain Assessment of Sphygmomanometer and the 12-Item Short Form Health Survey will be used to evaluate the symptoms and quality of life improvement at the baseline and the end of treatment. The Self-rating Anxiety Scale and the Self-rating Depression Scale will be used at the baseline and the end of treatment to investigate the influence of emotional state on brain activity and clinical variable. To ensure the consistency of acupuncture manipulation, the *deqi* scale will be performed after each acupuncture treatment. During the procedure of outcome evaluation and data analysis, the evaluators and statisticians will be blinded to the group allocation. The repeated measures analysis of variance (3 groups × 2 time points ANOVA) will be employed to analyze numerical variables of the clinical and neuroimaging data generated in the study, then the *t* test will be used in the post-hoc analysis.

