KOA is a complex, chronic pain condition partly due to both nociceptive and neuropathic mechanisms [13]. Previous studies have demonstrated that central sensitization, a pathological change in the central nervous system, plays an important role in the pathogenesis of KOA [14, 15]. With the widely application of neuroimaging techniques in pain research, investigators not only mapped the brain regions which are involved in the central pathogenesis of chronic pain, but also partly explored the central mechanism of acupuncture-induced analgesia by detecting the cerebral responses elicited by acupuncture. Using resting-state functional magnetic resonance imaging (rs-fMRI), researchers found that the patients with chronic pain demonstrated altered functional connectivity (FC) of the medial prefrontal default-mode network (DMN) and a changed regional homogeneity (ReHo) value of the anterior cingulate cortex (ACC) [16–18]. These results greatly enhanced the understanding of the central mechanism of chronic pain and have provided an approach to investigating the mechanism of acupuncture-induced analgesia. For instance, a functional magnetic resonance imaging (fMRI) study has shown that acupuncture can regulate the descending pain-modulatory system of KOA patients by enhancing the FC between the right frontoparietal network (rFPN) and the medial prefrontal cortex (mPFC) [19]. However, the sample size (only 10 in each group) and the dosage of acupuncture treatment (six acupuncture treatments for 4 weeks) of that study were relatively small, and the self-healing tendency of KOA patients could not be excluded due to the lack of waiting-list control.

So, this study aims to (1) investigate the influence of verum acupuncture treatment on the brain activities of patients with KOA compared with that of sham acupuncture treatment and waiting list patients by using fMRI with a larger sample size (36 patients in each group) and (2) analyze the possible correlations between the changes of cerebral activity and the improvement of clinical variables in each group, so as to explore how acupuncture manages pain by modulating brain function.

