## Methods/design

### Study design

This is a randomized controlled, parallel neuroimaging study, with participants and assessor blinded to the group assignment. A total of 108 participants diagnosed with KOA in accordance with American College of Rheumatology (ACR) criteria (1991 revised version) [20] will be considered as eligible patients. They will be randomly allocated into three equal groups with 36 patients in each group, including a verum acupuncture group, a sham acupuncture group and a waiting-list group. The treatment period will last for 2 weeks. Outcome measurements and MRI scan will be assessed at baseline and at the end of treatment (Figs. 1 and 2). The changes of clinical variables and cerebral activity of each group will be analyzed after data collection.

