### Data analysis

Before the data analyses, the research group will provide a statistical scheme to the statisticians. The scheme will include the required data and processing method. The data analysis process according to the scheme will be completed by statisticians who are independent from the research team and blinded to the test settings.

For the clinical data, statistical analyses will be performed with SPSS 22.0 statistics software (IBM Corp, Armonk, NY, USA). For the fMRI data, preprocessing and functional connectivity analysis will be performed by SPM12 software (SPM12, Wellcome Department of Imaging Neuroscience, London, UK; http://www.fil.ion.ucl.ac.uk/spm/) performing on MATLAB 8.6 (Mathworks, Inc., Natick, MA, USA) .

Both between and within groups, the numerical variables include the clinical data collected from the VAS, the short form of the McGill Pain Questionnaire, the WOMAC, ATS, SAS, SDS, PAS, *deqi* scale and the SF-12 scale, and Fisher’s transformed z value by functional connectivity analysis on neuroimaging data. Since there are three groups (verum acupuncture group, sham acupuncture group and waiting-list group) with two time points (pre-treatment and post-treatment), the repeated measures analysis of variance (ANOVA) will be employed to analyze both the clinical and neuroimaging data generated by the present study design. In the 2 × 3 group factorial design, the dependent variables were the clinical/neuroimaging data collected from pre-treatment and post-treatment, and data in the three different conditions (groups) will serve as the independent variable. Then, *t* tests will be used in the post-hoc analysis. The chi-square test will be used for categorical variables. All data are presented as the mean ± standard deviation (SD). Data are analyzed following intention to treat. A two-sided test is applied for available data and *P* < 0.05 is considered statistically significant. Finally, the Pearson’s correlation between the changes of cerebral activity and the improvement of clinical variables will be performed in each group.

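### Brain connectivity is the stated focus and the basis of the sample size, but it has no outcome level and shares a blanket P < 0.05 with the clinical scales

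*Protocol article*

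**What the plan says.** **Purpose.** The Abstract (Methods/design) of the protocol article states: "This study will focus on detecting the cerebral functional connectivity changes elicited by acupuncture treatment". The first aim, in the Background, reads: "investigate the influence of verum acupuncture treatment on the brain activities of patients with KOA compared with that of sham acupuncture treatment". The waiting list is the other comparator. The second aim is to correlate cerebral change with clinical improvement.

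**Sample size.** This section reasons from group sizes in MRI studies and from the team's experience with brain network analysis. It settles on 30 evaluable patients per group and raises this to 36 for dropout and head motion. It gives no effect size, standard deviation or power for any pain scale or connectivity measure.

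**Outcome measurement.** "The primary outcome measurements are the Visual Analog Scale" and the SF-MPQ. The secondary outcomes are WOMAC, the Attention Test Scale, the sphygmomanometer pain assessment and the SF-12. Neither level contains an imaging measure. The Study design section likewise sets the scan beside the outcomes: "Outcome measurements and MRI scan will be assessed at baseline and at the end of treatment".

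**Data analysis.** Connectivity appears as the "transformed z value by functional connectivity analysis on neuroimaging data", in one list with nine scales. The whole list goes to a three-group, two-time repeated measures ANOVA followed by t tests, and two-sided P < 0.05 is the only threshold stated.

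**The concern.** The purpose and the size of the trial come from an imaging question, while the declared ranking of outcomes answers a clinical one. A reader of the final report could not tell whether a connectivity result was the main finding, a supporting finding or an exploratory one, because the plan never says.

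The shared threshold makes this matter more. A pain scale yields one score per patient per visit, whereas a connectivity analysis can yield many values. If each is judged at 0.05, some connection may cross the line by chance, and nothing in the outcome ranking marks it as less than the answer to the first aim. What is at stake is how firmly the mechanistic conclusion can be worded. The validity of the data collected is not in question.

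**Working it through.** **1. Where connectivity stands in each section**

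| Section | Subject | Status given to connectivity |
|---|---|---|
| Abstract, Methods/design | Connectivity change | Stated focus |
| Background, first aim | Brain activity, verum versus sham and waiting list | Main question |
| Sample size | MRI and network-analysis precedents | Basis of n |
| Outcome measurement | VAS and SF-MPQ primary; four further measures secondary | None |
| MRI data acquisition | Scan parameters | None |
| Data analysis | Fisher z in one list with nine scales | Tested, unranked |

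The first three rows treat brain function as the main question. The last three never assign it a level.

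**2. The plan's own figure**

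30 × (1 + 0.20) = 36 per group, and 36 × 3 = 108, as stated. Dividing instead, 30 / (1 − 0.20) = 37.5, which rounds up to 38. That is a minor separate matter. What counts here is that the base of 30 cannot be derived for VAS, SF-MPQ or connectivity, because no effect size is given. The sample size therefore does not show which outcome the trial was meant to test.

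**3. What a flat 0.05 could mean for imaging (illustration)**

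The article does not say how many connections or voxels will be tested. For k independent tests, the chance of at least one false positive is 1 − 0.95^k:

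- k = 10: 1 − 0.95^10 = 0.40
- k = 20: 1 − 0.95^20 = 0.64
- k = 45 (all pairs of ten networks, 10 × 9 / 2): 1 − 0.95^45 = 0.90

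The counts and the independence are both assumptions. Positively correlated connections would give lower values.

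**4. What correction would cost (illustration)**

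For one pairwise contrast with n = 30 per group, power ≈ Φ(d√(n/2) − z), where z is the two-sided critical value. At an assumed standardized difference d = 0.8, d√(n/2) = 0.8 × √15 = 3.10.

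- One connection, alpha 0.05: Φ(3.10 − 1.96) = 0.87
- Bonferroni over 10, alpha 0.005: Φ(3.10 − 2.81) = 0.61
- Bonferroni over 20, alpha 0.0025: Φ(3.10 − 3.02) = 0.53

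With one pre-named connection, 80% power needs d of about (1.96 + 0.84) × √(2/30) = 0.72. Naming a connection in advance therefore preserves power that a wide corrected search gives up.

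**The case against.** Several points on the other side stand, and they limit the claim.

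- **A test is planned.** A reader might infer that the first aim has no test at all. The Data analysis section does not support that: it specifies ANOVA on Fisher z, post-hoc t tests and correlations with clinical change. What is lacking is status, not a test.
- **The outcome section opens as a clinical one.** Its ranking may be meant only for clinical instruments, with imaging handled elsewhere. This explains part of the gap but does not close it, since no other section ranks connectivity.
- **Seed and correction may be specified elsewhere.** The Data analysis section promises the statisticians a scheme covering the required data and processing. A reader might infer that the network will be picked after the results are seen. The article does not show this, and the absence of a named seed is not itself a finding. An unseen scheme would not, however, alter the printed outcome ranking or the printed threshold.
- **An exploratory mechanistic study is legitimate.** The Background and Discussion do speak of exploring how acupuncture works. But connectivity is never labelled exploratory, and the Abstract hopes for evidence bearing on clinical use.
- **The pain scales serve the mechanism too.** They supply the clinical half of the correlations in the second aim, so they are not unrelated to the trial's purpose.
- **The percentages are not the trial's error rate.** A reader might take 40% to 90% as such, but the document supplies no number of tests.

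**Conclusion.** The concern holds in limited form. The stated focus, the first aim and the sample-size argument concern brain function and connectivity, while every ranked outcome is a clinical measure and connectivity has no level anywhere in the article. The planned connectivity test shares one unadjusted threshold with nine scales. As written, its results cannot be called confirmatory.

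This rests on the article's own outcome lists and threshold, not on anything left to an analysis plan. Its size cannot be given as a single number: the false-positive figures depend on assumed independent counts, and the power figures on an assumed effect. The documents do not support the further claims that aim 1 goes untested, that the connection will be chosen after the fact, or that a particular connection ought to be primary. The matter should be settled before unblinding. It affects what may be concluded, not whether the data are usable.

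**What to change.** In Outcome measurement, state connectivity's status before unblinding, in one of two ways:

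1. List a change in connectivity as the primary imaging outcome, with verum versus sham as the lead contrast. Fix the seed or network in the statistical scheme before any imaging data are seen, and say how this outcome stands beside the two primary pain scales. Which connection to name is the sponsor's choice. The frontoparietal to medial prefrontal finding cited in the Background is one candidate, not a requirement.
2. State that VAS and SF-MPQ are the confirmatory outcomes and that all connectivity results are exploratory.

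In either case, in Data analysis replace P < 0.05 for imaging with a family-wise or false-discovery corrected threshold across the connections or voxels tested. For a single pre-named connection and contrast, this leaves 0.05 unchanged.

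**Cost.** A dated amendment and matching registry wording, with no new patients or scans. Fewer connections will reach significance, and the mechanistic conclusion may have to be worded as exploratory. The first option carries a further cost: Trial status reports 89 recruited and 80 through the intervention, so a primary imaging outcome added now is a substantive late change. The amendment should record its date, its reason and that allocation was still blinded. The second option avoids that difficulty.

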### Data management and monitoring

The case report form (CRF) includes observation time points, scanning time points, outcome measures, adverse events and safety evaluations. The outcome assessors will be required to follow the requirements of the CRF and fill in the relevant information in a timely and accurate manner. Only outcome assessors have access to the CRFs and perform double-data entry. The Evidence-based Medicine Center of the university will be responsible for monitoring the study as well as the data every 3 months.

### Data analysis

Before the data analyses, the research group will provide a statistical scheme to the statisticians. The scheme will include the required data and processing method. The data analysis process according to the scheme will be completed by statisticians who are independent from the research team and blinded to the test settings.

For the clinical data, statistical analyses will be performed with SPSS 22.0 statistics software (IBM Corp, Armonk, NY, USA). For the fMRI data, preprocessing and functional connectivity analysis will be performed by SPM12 software (SPM12, Wellcome Department of Imaging Neuroscience, London, UK; http://www.fil.ion.ucl.ac.uk/spm/) performing on MATLAB 8.6 (Mathworks, Inc., Natick, MA, USA) .

Both between and within groups, the numerical variables include the clinical data collected from the VAS, the short form of the McGill Pain Questionnaire, the WOMAC, ATS, SAS, SDS, PAS, *deqi* scale and the SF-12 scale, and Fisher’s transformed z value by functional connectivity analysis on neuroimaging data. Since there are three groups (verum acupuncture group, sham acupuncture group and waiting-list group) with two time points (pre-treatment and post-treatment), the repeated measures analysis of variance (ANOVA) will be employed to analyze both the clinical and neuroimaging data generated by the present study design. In the 2 × 3 group factorial design, the dependent variables were the clinical/neuroimaging data collected from pre-treatment and post-treatment, and data in the three different conditions (groups) will serve as the independent variable. Then, *t* tests will be used in the post-hoc analysis. The chi-square test will be used for categorical variables. All data are presented as the mean ± standard deviation (SD). Data are analyzed following intention to treat. A two-sided test is applied for available data and *P* < 0.05 is considered statistically significant. Finally, the Pearson’s correlation between the changes of cerebral activity and the improvement of clinical variables will be performed in each group.

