### Quality control is the precondition for the reliability of results

To improve the result reliability of this study, we designed the quality control program from the following aspects: (1) baseline homogeneity: patient selection for the influence of age and handedness on cerebral function and structure have long been investigated, this study restricts the participants to age between 40 to 60 years and to being right-handed; (2) acupuncture manipulation: in this study, all researchers will be trained to well understand the design and process of the trial, the use of the CRF, as well as measurements of quality. To avoid the manipulation difference, two veteran acupuncturists, who received special and standardized training before the trial, carry out all the treatment with the standard operation procedure. In addition, superfluous communication between acupuncturists and patients during acupuncture is forbidden. Besides, trained outcome assessors will be blinded to group allocation and responsible for the outcome assessment; (3) fMRI scan: to ensure the stability of MRI data acquisition, only one technician will perform all scans in the same MRI machine according to the related operation standard and the design of the study in the fixed condition. Furthermore, the unified guidebook will be used to standardize the opinions and behaviors of the researchers. Moreover, during the 24 h before scanning, participants will be asked to maintain their regular lifestyle and avoid overexertion and staying up late. The use of alcohol, tobacco, tea and coffee is prohibited. Before being scanned, the emotional state of each participant will be evaluated via the emotional state assessment scales. During the scan, participants will be asked to close their eyes and use a blindfold and to plug their ears with earplugs, stay awake and not speak; (4) *deqi*: considering the importance of the *deqi* sensation for the acupuncture effect, the needle sensation scale (*deqi* scale) will be measured after each treatment to evaluate the stimuli and *deqi* sensation in the process, which will help to exclude the bias of *deqi*.

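### The deqi scale is listed for the three-group, pre/post ANOVA, but it has no baseline value and no waiting-list value, so that ANOVA cannot be run for deqi

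*Protocol article*

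**What the plan says.** Under Data analysis, the protocol article lists the numerical variables to be examined between and within groups. The list starts with the VAS and the short-form McGill questionnaire, continues with "the WOMAC, ATS, SAS, SDS, PAS, *deqi* scale and the SF-12 scale", and ends with the connectivity z values. The next sentence takes as its ground that there are "three groups (verum acupuncture group, sham acupuncture group and waiting-list group) with two time points (pre-treatment and post-treatment") and states that "the repeated measures analysis of variance (ANOVA) will be employed to analyze both the clinical and neuroimaging data generated by the present study design". The sentence after that says that "the dependent variables were the clinical/neuroimaging data collected from pre-treatment and post-treatment". The Abstract applies the same 3 × 2 ANOVA to the numerical variables. Neither place makes an exception for deqi or gives it another analysis.

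Two other sections fix when and in whom deqi can be observed. Under Outcome measurement, "the *deqi* scale will be performed after each acupuncture treatment", and the scale is described as a rating of needle sensations. Under Waiting-list group, "participants will receive no treatment within 2 weeks". The legend of Fig. 1 agrees: 10 sessions in each acupuncture arm and no acupuncture in the waiting-list arm.

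The discussion of quality control says what the measurement is for. Deqi is rated after each treatment to evaluate the stimulation and the sensation, "which will help to exclude the bias of" deqi.

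**The concern.** The analysis named for deqi needs a value before and after treatment in each of three arms. The measurement schedule supplies neither a value before treatment nor any value in one of the arms. This is more than a detail left open for a later document: the article places the variable in a model that its own schedule rules out.

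What is at stake is limited but real. Verum and sham differ in point location and share the needling procedure, so the reading of a verum–sham difference in brain connectivity depends partly on whether needle sensation was similar in the two arms. Deqi is the recorded score that bears on this, and the quality-control text relies on it. As the text stands, that score has no analysis that can be carried out. Someone would have to decide later which of up to 10 sessions counts, or how to combine them, possibly after seeing the data.

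**Working it through.** The plan states no sample size, power or other figure for the deqi analysis, so there is none to reproduce. The check is whether the stated model can be estimated from the data that the schedule produces.

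**Inputs**
- Groups: 3, with 36 patients each, 108 in all (Study design).
- Time points in the ANOVA: 2, pre- and post-treatment (Data analysis).
- Needling sessions: 5 per week × 2 weeks = 10 in the verum arm, with the same procedure in the sham arm (Interventions); 0 in the waiting-list arm (Fig. 1 legend; Waiting-list group).
- Deqi timing: after each session (Outcome measurement).

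**Step 1: which cells can be filled**

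| Arm | Pre-treatment | Post-treatment |
|---|---|---|
| Verum | none, no needling yet | yes |
| Sham | none, no needling yet | yes |
| Waiting list | none | none, no needling |

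The design has 3 × 2 = 6 cells, and 2 can hold deqi data. Pre/post pairs: 0 of 108 patients. Waiting-list values: 0 of 36 patients.

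**Step 2: what can be estimated**

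With verum and pre-treatment as reference, write the cell mean as

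mean(g, t) = μ + α_g + τ·t + γ_g·t, with t = 0 before and 1 after treatment.

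This has 1 intercept, 2 group terms, 1 time term and 2 group-by-time terms, 6 parameters in total. With all six cells filled, the design matrix has rank 6 and every parameter is estimable. With only the two available cells the rank is 2:
- verum, post: μ + τ
- sham, post: μ + α_sham + τ + γ_sham

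None of the six parameters can be estimated on its own. In particular, the time effect and both group-by-time terms, which are what the repeated-measures ANOVA is meant to test, are not identified. The only between-arm contrast available is sham minus verum after treatment, α_sham + γ_sham.

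**Step 3: could the time points be redefined?**

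Suppose the first session were treated as pre and the last as post. Four of six cells would then be filled, because the waiting-list arm would still be empty. The model would use 2 of 10 sessions, and the first score would itself be a post-needling value. This is a different analysis from the one stated.

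**Step 4: what data exist**

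2 arms × 36 patients × 10 sessions = 720 session records at most, all of them post-session. They support a verum-versus-sham comparison.

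**The case against.** The best defence is that the sentence naming deqi only lists numerical variables, to separate them from the categorical ones that get a chi-square test. The ANOVA is then defined by data collected before and after treatment, so deqi would fall outside it by definition. The section also says that a statistical scheme with the required data and processing method will go to the statisticians, and a condensed article need not set out a separate deqi model. It is fair to say that the absence of such a model would not by itself be a finding. But the article does assign a method. The list leads straight into the ANOVA, the Abstract repeats it for the numerical variables, and no other treatment of deqi appears. The wording is wrong as it stands, and a scheme that followed it would carry the error forward.

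A second defence is the general sentence under Outcome measurement that all measurements are made at baseline and at the end of treatment. It does not help. The same section gives deqi its own per-session schedule, and needle sensation cannot be rated before or without needling. The verum acupuncture that waiting-list patients may be offered comes after their two weeks of observation, so it supplies no values within the study period.

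A reader might also infer more than the documents support:
- *That zeros would be entered for the waiting list.* Nothing in the article suggests this.
- *That a non-significant P value would be taken as proof that the arms were comparable.* The article gives the purpose as consistency of manipulation and exclusion of deqi bias. It does not state that inference.
- *That deqi is the only safeguard against unequal stimulation.* It is the described measurement of needle sensation, but stimulation is also controlled by design: the same method in both needling arms, two specially trained acupuncturists and a standard operating procedure.

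**Conclusion.** The point holds for the deqi scale and for nothing else. Two of six cells can hold data, no patient has a pre/post pair, and one of the three groups (36 of 108 patients) has no values, so the 3 × 2 repeated-measures ANOVA cannot be run for deqi. This follows from the article's own schedule and depends on no assumption about effect size, variance or dropout. The figure of 720 records is an upper limit that assumes every patient in both needling arms attends and is rated at all 10 sessions.

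It would be wrong to conclude that the trial's main analysis fails. The VAS, the short-form McGill questionnaire and the secondary outcomes are scheduled at baseline and end of treatment in all three arms, as are the MRI scans, so the ANOVA is feasible for them. Deqi is neither a primary nor a secondary outcome. The consequence is confined to the needle-sensation check that the quality-control text relies on. The text should be corrected before analysis.

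**What to change.** Remove the deqi scale from the variables assigned to the three-group, two-time-point ANOVA under Data analysis, and make clear that the Abstract's statement does not cover it. Add a separate sentence: deqi will be compared between verum and sham only, using the post-session scores (up to 10 per patient), and the between-arm difference will be reported with its 95% confidence interval. Either of two methods would do, provided one is named in advance:
- a repeated-measures or mixed model with arm and session, which uses every session and allows for correlation within patients;
- a two-group comparison of each patient's mean score over sessions, which is simpler.

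A term for acupuncturist and a margin for judging comparability are optional. The article gives no basis for choosing a margin, and it does not say how the two acupuncturists are divided between the arms.

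The cost is wording only. The scores are already collected at each session, and the Trial status section shows recruitment still open, so the change can be made before the data are analysed.
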